### Implementation {16c}

The randomisation database on Microsoft Lists will be prepared by the data manager who is unmasked throughout the trial. The EUC specialists will access the virtual envelopes to enrol participants online, as described above. Once the virtual envelope is unlocked, the EUC specialist will read the text displayed inside the envelope and describe the next steps depending on the allocation of the participant. The EUC specialists will also deliver the EUC online to all of those who are enrolled. Given that all procedures will be conducted remotely, we do not expect any accidental unmasking to take place for the outcome assessors, principal investigators (PIs) or others who are masked.

## Assignment of interventions: masking

### Who will be masked? {17a}

The PI (DF), site PI (SB), co-investigators and outcome assessors will be masked to treatment allocation during the trial. The trial statistician will be masked until the primary analysis is complete. Participants, facilitators, EUC specialists, qualitative researchers and the research director will be unmasked. The field team lead and data manager will also be unmasked as the data manager is responsible for developing the virtual envelopes through Microsoft Lists and the field team lead is responsible for the overall research assistant team support and supervision, carrying out routine data checks and monitoring.

### Procedure for unmasking if needed {17b}

There is no planned procedure for intentional unmasking in this trial. To prevent unintentional masking, all teams have been trained on carrying out the masking procedures, including standard operating procedures. If masking becomes compromised during outcome assessment, the outcome assessor will stop the assessment and notify the research director so a new outcome assessor can conduct the rest of the assessment. The primary outcome will be measured early in the outcome assessment to minimise the likelihood of it being compromised. Furthermore, outcome assessors may become unmasked when detecting an AE or SAE. If the participant remains part of the trial, a new outcome assessor will be assigned (see Sect. 22 for further information on management of AEs and SAEs).

## Data collection and management

### Plans for assessment and collection of outcomes {18a}

Quantitative and sociodemographic data for the CHANGE project will be collected by outcome assessors using ODK on password-protected tablets at baseline and at the 3-month follow-up (see Table 2). Each assessor will use an individual, password-protected tablet assigned specifically to them for completing the screening and outcome assessments. Data will be encrypted and uploaded to the ODK servers at the end of each working day. Daily data checks, including the number of records uploaded, will be conducted, and weekly data reports, which include variable summaries and a summary of missing data, will be generated by the field team lead. Participants will be assigned a unique participant ID to ensure consistent identification across all timepoints. Qualitative interviews will be conducted via the participants’ chosen platform (i.e. Zoom, telephone) in their chosen language (Ukrainian or Russian spoken in Ukraine) and audio recorded for transcription.

### Plans to promote participant retention and complete follow-up {18b}

Participants will be monitored throughout the trial by the field team lead using their unique participant IDs generated through Microsoft Lists Enrolment Database stored on NaUKMA SharePoint with limited access to particular team members who are unmasked. If participants miss an outcome assessment or a CHANGE session, up to three follow-up attempts will be made using their preferred method of contact, including Telegram, Viber, WhatsApp or other. Up to three attempts will also be made to follow up with participants who drop out and those who are lost to follow up at the 3-month outcome assessment.

### Data management {19}

Data will be collected through the ODK platform by the outcome assessors, who will fill in the ODK survey (data) whilst they are on the call with the participant. The ODK server is hosted by the London School of Hygiene and Tropical Medicine and encrypts the data that is stored. A unique participant ID is created automatically by Microsoft Lists Enrolment Database, which will be used to track the participant throughout the trial. The participant ID will be linked to the participants’ name through a password protected database stored on Sharepoint. This Sharepoint will only be accessible to those on the CHANGE team who are unmasked throughout the trial. There are standard operating procedures in place for data entry, monitoring and review and all team members will be given training on these components.

To prevent data loss, a copy of the data will be kept on external hard drives at NaUKMA office (managed by the field team lead) and on SharePoint. The folders and files with the research data stored on the hard drive will be secured by passwords and kept in locked cabinets. Weekly data checks will be carried out by the field team lead including review of the order of randomisation, data entry and range checks. If a data error is found, it will be addressed and logged by the field team lead following the data management plan to ensure there is evidence of changes made.

Sharing of the anonymised and encrypted ODK data will take place using the password protected Sharepoint. The data will not be made available through an open data repository due to the safety and conscription concerns of participants noted during the feasibility trial.

The qualitative data will be audio recorded by the researcher who conducts the interview, and transcription will be done by an external company that has appropriate experience and expertise. Once the data has been transcribed and anonymised, the audio recordings will be deleted. Any data to be used for publication and dissemination will be anonymous and participants will be asked to consent to this.

### Confidentiality {27}

Participants will be assigned with a unique participant ID at the time of registration for participation in the trial which will be automatically generated through Microsoft Lists Enrolment Database stored on Sharepoint. All the information provided by the participant will be saved on the encrypted ODK server and transferred to the password protected Sharepoint. The data management and data security will be aligned to the requirements of General Data Protection Regulations (GDPR). All team members will be trained on maintaining the confidentiality of the participants and protection of the qualitative and quantitative data.

### Plans for collection, laboratory evaluation and storage of biological specimens for genetic or molecular analysis in this trial/future use {33}

This trial does not involve collecting biological specimens for storage or evaluation.

## Statistical methods

### Statistical methods for primary and secondary outcomes {20a}

In line with the protocol published by van der Boor et al. [23], a statistical analysis plan will be written by the statistician based at the London School of Hygiene and Tropical Medicine and approved by the Data Safety and Management Board (DSMB) prior to unmasking of the data and analysis. The quantitative data will be analysed using Stata 17.0. An initial analysis will be conducted to compare participants who did and did not provide consent for participation following initial screening. Further descriptive analysis will then be carried out to compare the baseline characteristics of the participants. If substantial baseline imbalances exist in characteristics that are likely to affect outcomes, these will be adjusted a priori to the outcome analyses.

Binary outcomes will be analysed using logistic regression or negative binomial regression, depending on the distribution. Marginal standardization and delta methods [38] will be used to calculate adjusted risk ratios if logistic regression is used. Continuous outcomes will be analysed using linear regression, and adjusted mean differences reported. Before analysis, distributions of all outcome variables will be inspected, and if necessary, transformations or other modelling options will be considered.

All models will be adjusted for baseline characteristics that differ between the arms as determined by the descriptive analysis and the baseline measures. *P* values will not be used to identify differences between arms at baseline, as these are assumed to be at random. Fully adjusted (if appropriate) model results will be presented and reported using CONSORT guidelines [39]. Intention to treat principles will be used for the primary analysis.

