**Secondary outcomes**		
Percentage days of heavy drinking	TLFB	X
Alcohol Misuse	• Alcohol Use Disorders Identification Test (AUDIT) [26] • Alcohol, Smoking and Substance Involvement Screening Test (ASSIST) [32]	X
Psychological distress	Kessler-10 (K10) [27]	X
Depression	Mental Health Assessment Inventory (MHAI), depression sub-scale [33]	X
Anxiety	Mental Health Assessment Inventory (MHAI), anxiety sub-scale [33]	X
PTSD	Mental Health Assessment Inventory (MHAI), PTSD sub-scale [33]	X
Functional disability	Mental Health Assessment Inventory (MHAI) [33]	X
Perpetration of intimate partner violence	United Nations Multi-Country Study on Men and Violence [34]	X
Health economics indicators	• EuroQol 5 dimensions 5 Levels (EQ-5D-5L) [42] • Subjective wellbeing [35] • Oxford Capabilities Mental Health questionnaire (OxCAP-MH) [36] • User cost questionnaire	X

**Table 3 Tab3:** Details on CHANGE Intervention Trial Outcome Measures (table adapted from Van Der Boor et al., 2024 [23])

Instrument	Description	Outcome	Contextual validity
Timeline Followback	Diary method to retrospectively assess daily estimates of drinking	Percentage days abstinent (PDA): Proportion of past 14 days on which participant was abstinent; analysis based on distribution. It also allows measurement of percentage of days of heavy drinking	Validated for alcohol use assessment including in Ukraine [43]
AUDIT	Ten-item questionnaire to measure alcohol intake, identify potential dependence on alcohol; and experiences of alcohol-related harm. Each item assessed on a scale of 0 to 4	Mean score, and dichotomous (medium vs. high risk) as secondary outcome	Validated for the current project with Ukrainian and Russian speaking men living in Ukraine, paper forthcoming
ASSIST	Eight-item screening questionnaire on estimates of alcohol use, tobacco products, and other drugs across the lifetime and in the past three months. Measured on a scale of 0 to 7	Mean score	Validated in a multisite international study covering Australia, Brazil, India, Thailand, United Kingdom, USA, and Zimbabwe [44]
K10	Ten-item scale on non-specific psychological distress, scored on a scale of 1 to 5	Mean score	Validated in Ukraine including amongst war-affected Ukrainians [45, 46]
MHAI	Thirty-two item scale on depression, post-traumatic stress, anxiety, functioning and alcohol use	Mean score	Locally validated measure with good psychometric properties [33]

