United Nations Multi Country Study on Men and Violence	Eleven items are used to measure the prevalence of perpetration of violence in the last 3 months. The items are assessed on a scale of 1 to 4, or 1 to 7	Prevalence of IPV split by type of intimate partner violence (physical, sexual)	Previously validated in Bangladesh, China, Cambodia, Indonesia, Sri Lanka, and Papua New Guinea [34]
EQ-5D-L	Five item questionnaire for measuring health related quality of life across five dimensions: mobility, self-care, usual activities, pain/discomfort, and anxiety/depression, rated on the day. A five-level response option is used	Locally adjusted scoring algorithm	Validated across different contexts including Ukraine (https://euroqol.org/register/obtain-eq-5d/available-versions/)
Subjective Wellbeing	Five items on subjective wellbeing, measuring overall life satisfaction, whether the things the respondent does are worthwhile, and affect; scored on a scale of 1 to 5	Locally adjusted scoring algorithm	Used across countries in the Gallup world poll which covers more than 150 countries, including Ukraine (https://www.gallup.com/analytics/349487/world-happiness-report.aspx)
OxCAP-MH	Sixteen item index on wellbeing, covering various domains of individual well-being including overall health, enjoying social and recreational activities, friendship, and support, having suitable accommodation etc. Scored on a scale of 1 to 5	Mean score	Has been contextually translated and validated by the current research team in Ukraine into Ukrainian and Russian spoken in Ukraine (publication forthcoming)
User Cost Questionnaire	Fifteen item measure on household expenditure specifically designed for this trial to measure the opportunity cost of participating in the CHANGE intervention	The opportunity cost of participating in the CHANGE intervention	Specifically designed and piloted for this trial. Based on the iMTA productivity loss of cost questionnaire

**Table 4 Tab4:** Sociodemographic data collection

Construct	Measure
Education	Education (no school, primary, secondary, tertiary education, etc.)
Age	In years
Socio-economic status	Self-perceived relative socio-economic status (e.g., income level as multiple-choice question)
Trauma exposure	Life Events Checklist
Use of local substances (e.g., khat, tobacco, marijuana, opioids, synthetic drugs etc.)	Measured developed for study or standardized measure (e.g., ASSIST)
Displacement status	Multiple-choice answer

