### Sample size {14}

A sample size of 500 enrolled participants (250 in each arm with 1:1 allocation) will provide 90% power (alpha = 0.05) to detect a difference in participants’ PDA from alcohol at follow-up of 55% in the EUC arm vs 68% in the CHANGE arm. This assumes participants’ PDA from alcohol is distributed with a standard deviation of 37% in both arms [37]. Both the effect size and the standard deviation are based on the Counselling for Alcohol Problems (CAP) trial (54% vs. 69%). The sample size calculation accounts for 20% loss to follow-up at 3 months and is based on Nadkarni et al. 2017 [37].

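### Negative binomial regression is offered for the binary secondary outcomes, where the stated criterion decides nothing and the model's default standard errors are too large

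*Protocol article*

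**What the plan says.** Section 20a of the protocol article sets the models by outcome type. For binary outcomes it says: "Binary outcomes will be analysed using logistic regression or negative binomial regression, depending on the distribution". The next sentence covers the effect measure on one of the two routes: "Marginal standardization and delta methods [38] will be used to calculate adjusted risk ratios if logistic regression is used". Continuous outcomes go to linear regression. The section names no model for counts. It adds a general allowance that "distributions of all outcome variables will be inspected, and if necessary, transformations or other modelling options will be considered".

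Table 3 shows which outcomes are binary. AUDIT is reported as "Mean score, and dichotomous (medium vs. high risk) as secondary outcome", and perpetration of intimate partner violence as a prevalence, separately for physical and sexual violence. Both are secondary. The primary outcome, percentage of days abstinent, is not binary; Table 3 defines it as "Proportion of past 14 days on which participant was abstinent; analysis based on distribution".

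The protocol gives no expected event rate for either binary outcome and does not say which variance estimator the negative binomial route would use.

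**The concern.** Negative binomial regression is a model for counts that vary more than a Poisson distribution allows. A 0/1 variable is fully described by its prevalence and always varies less than Poisson. Looking at its distribution therefore cannot point to negative binomial, and the stated criterion leaves the choice of model open after the data have been seen.

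If that route were taken with default standard errors, confidence intervals for the risk ratio would be too wide and p-values too large. A real effect on partner violence, which is one of the stated secondary hypotheses, or on dichotomised AUDIT could be missed. The error does not favour the intervention.

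**Working it through.** The protocol states no power or event rate for a binary outcome, so there is no figure of its own to reproduce here. The inputs are:

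- Analysed per arm: 250 enrolled less 20% loss (Sample size, item 14), so 250 × 0.80 = 200.
- Test: nominal 0.05, taken as two-sided. The protocol does not state sidedness.
- Control event rate p0: not given, so a range is shown as an assumption.
- Effect: for each p0, the lower rate p1 that has 80% power under the correct variance (an assumption).

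**Step 1: the dispersion goes to zero.** Negative binomial assumes variance μ + αμ², with α not below 0. Binary data have variance μ(1 − μ), which is less than μ, so the best-fitting α is at its boundary. In one simulated data set (50% vs 36%, 200 per arm) the log-likelihood was −311.28 at α near 0, −314.78 at α = 0.1 and −342.57 at α = 1. A fit with α left free, on simulated binary data, returned α = 0.00007 and no standard errors because the Hessian could not be inverted. The figures below therefore describe the Poisson limit of the model.

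**Step 2: size of the standard error.** For the log risk ratio with n per arm:

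- Correct: SE² = (1 − p0)/(n·p0) + (1 − p1)/(n·p1)
- Model-based at α = 0: SE² = 1/(n·p0) + 1/(n·p1)

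With no effect (p0 = p1 = p) the ratio of model-based to correct SE is 1/√(1 − p), which is 1.05 at p = 0.10, 1.20 at 0.30 and 1.41 at 0.50. The actual type I error is 2[1 − Φ(1.96/√(1 − p))], which is 0.039, 0.019 and 0.006 at those rates. All are below 0.05.

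**Step 3: power.** Power with model-based SEs = Φ[(|log(p1/p0)| − 1.96 × SE_model)/SE_correct]. At p0 = 0.50, p1 = 0.359: |log(0.359/0.50)| = 0.331; 1.96 × 0.155 = 0.304; (0.331 − 0.304)/0.118 = 0.23; Φ(0.23) = 0.59.

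| p0 | p1 | Correct SE | Model-based SE | Power, correct | Power, model-based | Loss (points) |
|---|---|---|---|---|---|---|
| 0.10 | 0.026 | 0.483 | 0.494 | 80% | 79% | 1 |
| 0.20 | 0.097 | 0.258 | 0.277 | 80% | 76% | 4 |
| 0.30 | 0.178 | 0.186 | 0.212 | 80% | 72% | 8 |
| 0.50 | 0.359 | 0.118 | 0.155 | 80% | 59% | 21 |
| 0.70 | 0.563 | 0.078 | 0.127 | 80% | 35% | 45 |

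**Step 4: simulation check.** 1,000 trials per scenario, 200 per arm, α held near zero for the negative binomial fits.

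| Rates | Logistic | Negative binomial, model-based SE | Negative binomial, robust SE |
|---|---|---|---|
| 10% vs 3.5% | 74% | 71% | 74% |
| 30% vs 18% | 79% | 70% | 79% |
| 50% vs 36% | 80% | 57% | 80% |

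The simulation agrees with the formula. It also shows that the loss comes entirely from the variance estimator, because robust standard errors restore the power of logistic regression.

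**The case against.** The strongest reply is that the harm needs three things at once: the negative binomial route is taken, its model-based standard errors are used, and the outcome is common. Logistic regression is named first, other models are allowed, and a fit that returns no standard errors would probably send the analyst back to logistic regression. The variance estimator is a detail that the separate statistical analysis plan may properly settle. All of this stands, and it limits the size of the problem.

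A second reply is that the model was meant for counts. Section 20a has no count model, and Table 3 uses similar language about distributions for an outcome built from days out of 14. That is plausible, and the documents cannot settle it. If it is so, the sentence attaches the model to the wrong type of outcome and still needs correcting.

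A reader might also infer that the negative binomial route lacks a correction because marginal standardisation is tied to logistic regression. The text does not support that. Marginal standardisation turns logistic output into risk ratios and does not repair standard errors. A log-link model gives a ratio directly, so restricting that step to the logistic route is coherent.

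Deferral to the analysis plan does not remove the point, because the issue is a rule that the protocol states. The allowance for other modelling options does not withdraw that rule.

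**Conclusion.** The sentence is wrong as written: it offers a count model for 0/1 outcomes under a criterion that cannot choose between the options. Nothing elsewhere in the protocol corrects it. The consequence is conservative and confined to secondary outcomes. The primary outcome and its sample size are unaffected, and AUDIT is also analysed as a mean score.

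A reader might infer that the plan will cost these outcomes substantial power. The documents do not support so general a statement, since they give neither event rates nor a variance estimator. With 200 per arm, two-sided 0.05, model-based standard errors and an effect with 80% power under the correct variance, the loss is about 1 point by formula at a 10% control rate (about 3 in simulation), 4 at 20%, 8 at 30% and 21 at 50%. With robust standard errors it is about zero. Nor do the figures support a reading that false positives would rise; the type I error falls.

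**What to change.** Delete negative binomial regression from the sentence on binary outcomes. State that binary outcomes will be analysed by logistic regression with marginal standardisation to risk ratios and delta-method standard errors, with Poisson regression and robust standard errors as the fallback if the logistic model does not converge. If negative binomial was intended for counts, such as drinking days, say so in a separate sentence for count outcomes.

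The cost is one or two sentences in the protocol and the matching lines of the analysis plan, agreed before unmasking. Data collection and sample size do not change.

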**Methods:**

This study is a parallel-arm, single-blind, individually randomised controlled trial across Ukraine government-controlled territories. Following informed consent, we will recruit 500 adult war-affected men, randomised 1:1 to EUC and CHANGE, or EUC alone. Inclusion criteria include elevated levels of alcohol use (between 8 and 19, inclusive, on the Alcohol Use Disorder Identification Test); psychological distress (≥ 16 on the Kessler Psychological Distress Scale) and ability to speak Ukrainian or Russian. CHANGE will be delivered over 6 weeks by 14 community-based facilitators, with outcomes assessed at 3 months post-randomisation. The primary outcome for CHANGE is the PDA from alcohol at 3 months, measured using the Timeline Follow Back. Secondary outcomes include percentage days of heavy drinking, alcohol misuse, psychological distress (depression, anxiety, and posttraumatic stress disorder), functional disability, intimate partner violence perpetration and health economics indicators at 3 months. The primary analysis will follow an intention-to-treat approach. A mixed-methods process evaluation will examine facilitator competency, recruitment, retention/completion, appropriateness, dose received, fidelity and feasibility of delivery and acceptability.

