### Intervention description {11a}

In addition to being offered EUC as described above, participants randomised to the intervention arm will be offered six sessions of the CHANGE intervention in a remote format. Based on the feasibility trial, an additional booster session may be included that focuses on reviewing the previously taught strategies (without introducing new ones) that can be provided to participants with high stress levels, providing extra time to practice and internalize them. A convenient online platform for the call will be agreed upon with the participants. These can include, but are not limited to, Zoom, Google Meets, Skype, Telegram or Viber.

The CHANGE intervention is a brief, transdiagnostic psychological intervention, informed by PM + and enhanced through strategies based on empirical evidence, which aim to address alcohol misuse [22, 23]. The initial PM + intervention uses strategies including problem solving, stress management, behavioural activation and accessing social support to address common mental health problems [18]. To develop the CHANGE intervention targeting alcohol misuse, firstly a meta-review was conducted [28] to identify evidence-based strategies for the management of AUDs. After this a systematic intervention adaptation process followed to incorporate strategies into PM + that address alcohol misuse including enhancing motivation to change drinking behaviours. CHANGE is composed of three phases each which include individual weekly sessions of approximately 90 min each with the facilitators (Table 1).

**Table 1 Tab1:** Outline of the three phases and psychological strategies included in each phase of CHANGE

Phase I	Phase II	Phase III
• Engaging the client • Assessments • Review from the assessments • Information about the CHANGE intervention • Understanding adversity • Understanding alcohol use • Goal setting for drinking • Specifying a change plan	• Changing drinking behaviours • Managing stress • Managing emotions • Managing problems • Behaviour activation • Strengthening social support	• Relapse prevention • Ending the intervention • Optional booster session
Basic helping and motivational skills		

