### Strategies to improve adherence to interventions {11c}

We recruited 4 licensed mental health care professionals (e.g. clinical psychologists, psychiatrists, experienced counsellors) who received a training-of-trainers program with the aim of carrying out supervision for CHANGE facilitators. These trainers/supervisors then delivered a 6-day in-person training, and 1-day online refresher training to the first cohort of facilitators ((*N* = 13, prior to the start of the trial), and a 7-day in-person training to the second cohort of facilitators (*N* = 9). The training program included education on common mental disorders, basic counseling skills, delivery of the CHANGE sessions and self-care. After the training, 16 facilitators were selected for the trial based on their skills, availability and/or geographical location. Two facilitators decided to discontinue their involvement, leaving 14 facilitators for the trial.

During the upcoming trial, the 14 CHANGE facilitators will be divided into two groups, with two supervisors being assigned to each group for online supervision (approximately 2 h per week per group). The supervisors will rotate on a weekly basis within their respective groups to ensure that each supervisor conducts two group supervisions per month, resulting in a weekly group-supervision opportunity for each facilitator. A gradual decrease in frequency of group supervisions is planned throughout the duration of the trial, dependent on the facilitators’ ongoing clinical competencies, decision-making skills, and adherence to protocols.

To carry out fidelity checks, participant sessions for fidelity assessments will be randomly selected by the statistician using Stata 18.0 (College Station, TX, USA) prior to the start of recruitment. An equal number of recordings will be randomly selected across all six sessions, with each participant recorded only once. The M&E lead tracks selected sessions for fidelity recordings on a weekly basis. During consent, participants explicitly give permission for session recordings for quality assurance. Fidelity checklists have been developed based on the strategies and components covered in each of the CHANGE sessions. Fidelity assessments will be completed by the trainers/supervisors.

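### The named regression models do not allow for facilitator clustering in the CHANGE arm; if outcomes vary by facilitator, type I error exceeds 5% for conclusions reaching beyond these 14 facilitators

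*Protocol article*

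**What the plan says.** **Delivery.** The abstract states: "CHANGE will be delivered over 6 weeks by 14 community-based facilitators, with outcomes assessed at 3 months post-randomisation". Section {11c} explains the number: "Two facilitators decided to discontinue their involvement, leaving 14 facilitators for the trial". Under Intervention description {11a}, "participants randomised to the intervention arm will be offered six sessions of the CHANGE intervention in a remote format", and the format is one-to-one: "CHANGE is composed of three phases each which include individual weekly sessions of approximately 90 min each with the facilitators". Enhanced usual care (EUC) is given by two specialists to everyone enrolled, in both arms (sections {6b} and {16c}), so it creates no clustering peculiar to one arm.

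**Analysis.** Section {20a} gives two rules: "Continuous outcomes will be analysed using linear regression, and adjusted mean differences reported", and "Binary outcomes will be analysed using logistic regression or negative binomial regression, depending on the distribution". Adjustment is for the baseline measures and for baseline characteristics found to be imbalanced. The only flexibility is that "distributions of all outcome variables will be inspected, and if necessary, transformations or other modelling options will be considered". The same section says that "a statistical analysis plan will be written by the statistician based at the London School of Hygiene and Tropical Medicine"; that plan is not shown.

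**Sample size.** Section {14} rests on a difference in percentage of days abstinent (PDA), a standard deviation, alpha, power and 20% loss. It gives no ICC or design effect.

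**The concern.** This is a partially nested design. Men in the CHANGE arm who share a facilitator may have more similar outcomes than men who do not, whereas men in the EUC arm have no such grouping. Ordinary linear or logistic regression takes each man as a separate piece of information. If facilitators differ in their results, the CHANGE arm holds less information than its head count suggests, and the model's standard error is too small.

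Some variation is plausible on the article's own facts. Ten facilitators are psychologists, two are psychology trainees, one is a social worker and one has no mental health background. They work in different regions and organisations, were trained in two cohorts with different formats, and are supervised in two groups.

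The error runs in one direction: confidence intervals too narrow and false positives too frequent. It would affect the primary outcome and any secondary outcome on which facilitators differ.

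**Working it through.** **Inputs from section {14}.** 250 enrolled per arm; 20% loss, so 250 × 0.8 = 200 analysed per arm; PDA 55% versus 68%, a difference of 13 points; SD 37 points; alpha 0.05, taken as two-sided because sidedness is not stated. There are 14 facilitators.

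**Assumptions not in the documents.** The ICC; equal caseloads; one facilitator per man.

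**1. The plan's own figure.** SE = 37 × √(2/200) = 3.70. Power = Φ(13/3.70 − 1.96) = Φ(1.55) = 94.0%, against the 90% stated. For 90% power, 171 analysed per arm suffice; 171/0.8 gives 214 per arm, or 428 enrolled, against 500. The stated 90% is therefore not reproduced, but the gap is on the safe side.

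**2. Effect of clustering in one arm.**
- Caseload: m = 200/14 = 14.3.
- Design effect in the CHANGE arm: DE = 1 + (m − 1) × ICC.
- Variance inflation of the difference: VIF = (1 + DE)/2.
- True SE over reported SE: √VIF.
- Type I error of the unclustered test: 2 × [1 − Φ(1.96/√VIF)].
- Power of a valid clustered test, normal approximation: Φ(13/(3.70 × √VIF) − 1.96).

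Example at ICC 0.05: DE = 1 + 13.3 × 0.05 = 1.66; VIF = 1.33; √VIF = 1.15; type I error = 2 × [1 − Φ(1.70)] = 9.0%.

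| ICC | DE | SE ratio | Type I error, formula | Type I error, simulated | Power if clustering handled, normal | Same, small-sample df (simulated) |
|---|---|---|---|---|---|---|
| 0 | 1.00 | 1.00 | 5.0% | 5.2% | 94.0% | 92.9% |
| 0.01 | 1.13 | 1.03 | 5.8% | 5.9% | 92.5% | 91.1% |
| 0.02 | 1.27 | 1.06 | 6.6% | 6.5% | 91.0% | 89.9% |
| 0.05 | 1.66 | 1.15 | 9.0% | 8.9% | 86.1% | 83.9% |
| 0.10 | 2.33 | 1.29 | 12.9% | 12.7% | 77.7% | 74.4% |

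The simulation used 20,000 runs per row and compared a plain t-test with a test on facilitator means using Satterthwaite degrees of freedom. The facilitator-level test held 4.9% to 5.2% throughout.

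**3. Unequal caseloads.** With a coefficient of variation (CV) of 0.5, DE = 1 + ((1 + CV²) × m − 1) × ICC. Type I error becomes 6.0% at ICC 0.01 and 10.0% at ICC 0.05.

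**4. How much clustering the surplus absorbs.** Tolerable VIF for 90% power = (13/3.70)² / (1.96 + 1.28)² = 1.175. Then ICC = 2 × (1.175 − 1)/(14.3 − 1) = 0.026. With small-sample degrees of freedom the limit is about 0.02 (89.9%).

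**The case against.** **The analysis plan is unseen.** Section {20a} names model families. It does not declare observations independent, and cluster-robust errors are compatible with linear regression. A reader might infer that the trial has decided to treat the men as independent; the article does not say so. What remains is that section {20a} fixes the models and the adjustment set, and ties its one escape clause to the shape of the outcome distributions, not to dependence. An analysis plan that carried out this text as written would leave the nesting unhandled.

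**No ICC is given.** A reader might infer that the standard errors are certainly too small and that type I error certainly exceeds 5%. That does not follow. At ICC 0 there is no inflation, at 0.01 to 0.02 it is modest, and nothing in the documents supports one value over another. Common training, group supervision, fidelity checks and competency assessment are meant to hold differences down. Men who attend few sessions would also dilute clustering under intention to treat. These points lower the likely size but do not remove the possibility.

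**Power.** A reader might infer that the trial is underpowered because section {14} has no design effect. The surplus in step 1 answers that for small ICCs, and the adjustment for baseline PDA, which these figures ignore, would usually help further. It does not answer the type I error.

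**Target of inference.** If conclusions concern only these 14 facilitators, benefit produced by a few good ones is a real average effect in this trial and not a false positive. The article does not state its target. However, its Discussion and Dissemination sections look to use in other regions and to scaling up, which fits the wider target.

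**Inferred premises.** That each man stays with one facilitator, and that the facilitator's identity is recorded for analysis, are natural readings but are not stated.

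**Conclusion.** The point holds conditionally. The design is partially nested and the named models make no allowance for it. If the facilitator ICC is above zero and inference is meant to reach beyond these 14 facilitators, the standard error of the treatment effect is understated and type I error exceeds 5%. Under the stated assumptions the inflation runs from negligible (5.8% to 6.0% at ICC 0.01) through modest (6.6% at 0.02) to serious (about 9% at 0.05 and 13% at 0.10). The figures are worked for a continuous outcome such as PDA. For binary outcomes the direction is the same but the size was not calculated. Power is not the main issue: the stated 90% holds to an ICC of about 0.02 to 0.026. This is a cheap improvement to make before unmasking, not a defect in the design.

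**What to change.** Before unmasking, specify as primary an analysis that allows for facilitator clustering in the CHANGE arm only. One suitable form is a partially nested mixed model with a facilitator random effect in that arm, each EUC man as his own cluster, arm-specific residual variance, and Satterthwaite or Kenward-Roger degrees of freedom. An equivalent method valid for 14 clusters would also serve. Give binary outcomes matching treatment. Record the facilitator assigned to each CHANGE participant, analyse by that assignment, and set a rule for men who withdraw before one is assigned. Report the facilitator ICC and keep the unclustered model as a sensitivity analysis.

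**Cost.** Analysis plan wording, one recorded variable and somewhat wider confidence intervals. With no clustering present, power moves only from 94.0% to about 92.9%. No increase in sample size is needed. If the ICC proved to be 0.05 or more, power would fall below 90%, and the wider interval would then be the honest one.

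One practical matter needs arranging. Facilitator identity exists only in the CHANGE arm, so a dataset that carries it reveals allocation, while section {17a} keeps the trial statistician masked until the primary analysis is complete. The model and code should be fixed before that variable is linked, or the final run done by someone already unmasked.
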